### Measurements

Immediately after providing digital informed consent for the SPRINT study, all participants are asked to fill out the baseline questionnaire. This questionnaire consists of six sections on demographics, training, running events, lifestyle, previous RRIs and health complaints. The items of these sections are described in table 1.

**Table 1 T1:** Items of the baseline questionnaire

Section	Items
Demographics	Sex
	Date of birth
	Height (cm)
	Weight (kg)
Training	Running experience (years)
	Running frequency (times per week)*
	Running time (hours per week)*
	Running distance (km per week)*
	Running speed (min per km)*
	Membership of a running club (yes/no)
	Use of training schedules (yes/no)
	Training surface (paved/unpaved and flat/non-flat)
	Types of training
	Endurance training (%)
	Interval training (%)
	Specific exercises (%)
	Shoe type (neutral/anti-pronation/minimalistic/unknown)
	Number of running shoes
	Advices on running shoes
	Use of bandages (yes/no)
	Use of sport compression socks (yes/no)
	Use of inlays (yes/no)
	Average cadence (steps per min)
	Foot strike pattern (rearfoot/midfoot/forefoot/unknown)
Running events	Previous participation (yes/no)
	Years of participation
	Average participations per year
	Year of last participation
	Distances of previous running events
Lifestyle	Smoking (yes/no)
	Alcohol consumption (average glasses per week)
	SQUASH questionnaire†
Previous running-related injuries	Running-related injury in previous 12 months (yes/no)
	Anatomical location (lower back/buttock/hip/groin/ventral thigh/dorsal thigh/knee/shin/calf/Achilles tendon/ankle/foot/toe)
	Diagnosis
	Onset (sudden/gradually)
	Duration of complaints (weeks)
	Still suffering injury (yes/no)
Health complaints	Presence (yes/no, and if yes, which health complaints)

*Asked for the averages over the last month and last year.

†Short questionnaire to assess health-enhancing physical activity, a validated questionnaire that measures health-enhancing physical activity in large populations.^48 49^

Three follow-up questionnaires are sent to the participants (1 month before, 1 week before and 1 month after the running event). These follow-up questionnaires mainly focus on RRIs (table 2).

**Table 2 T2:** Items of the follow-up questionnaires and injury questionnaire

Questionnaire	Section	Items
Follow-up questionnaire	Running-related injuries	Running injury since filling in previous questionnaire (yes/no)
		Location (lower back/buttock/hip/groin/ventral thigh/dorsal thigh/knee/shin/calf/Achilles tendon/ankle/foot/toe)
		Onset (sudden/gradually)
		Recurrent injury (yes/no)
		Type (bruise/muscle or tendon injury/sprain/distortion/ ligament injury/ bone fracture/joint dislocation/cartilage or meniscus injury/nerve entrapment/unknown)
		Diagnosis
		Suspected cause
		Severity (OSTRC Overuse Injury Questionnaire*)
		Treatment (yes/no, and if yes, what treatment)
		Use of (pain) medication (yes/no, and if yes, what medication)
		Pain and impairment of activities of daily living-tasks
		Complete recovery (yes/no)
		Duration of complaints (weeks)
	Running behaviour†	RAS questionnaire‡
	Training§	Average running frequency over last month (times per week)
		Average running time over last month (minutes per week)
		Average running distance over last month (km per week)
		Average running speed over last month (minutes per km)
	Injury prevention programme¶	Read programme (yes/no, and if yes, which steps)
		Applied programme to training (yes/no, and if yes, which steps)
Injury questionnaire	Running-related injuries	Date onset injury
		Location (lower back/buttock/hip/groin/ventral thigh/dorsal thigh/knee/shin/calf/Achilles tendon/ankle/foot/toe)
		Pain severity (0–10 Numerical Rating Scale)
		Severity (OSTRC Overuse Injury Questionnaire*)
		Complete recovery (yes/no)

*Oslo Trauma Research Centre Overuse Injury Questionnaire.^50^

†Only included in the first follow-up questionnaire (1 month before the running event).

‡Running Addiction Scale,^51^ translated into Dutch according to the existing guidelines,^52^ included to assess whether specific subgroups of runners are more prone to RRIs due to altered running behaviour are present.

§Only included in the second follow-up questionnaire (1 week before the running event).

¶Only included in the last follow-up questionnaire of the intervention group (1 month after the running event).

To obtain more detailed information about the moment of occurrence of new RRIs, participants are asked in biweekly newsletters to actively register their RRIs. The newsletters contain a hyperlink to an online injury questionnaire, which administers information about sustained RRIs (table 2). Next to the hyperlink to the injury questionnaire, the biweekly newsletters also contain updates on the SPRINT study (eg, on the number of included participants or one of the researchers introduces himself/herself) or general information about running. The biweekly newsletters for the intervention group also highlight the content of the prevention programme.

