### Outcome measures

The primary outcome measure of the SPRINT study is the difference in injury proportion between the intervention and the control group in the time period between the registration for the SPRINT study and 1 month after the running event. An RRI is defined as a self-reported injury of the muscles, joints, tendons and/or bones in the lower back or lower extremities (hip, groin, thigh, knee, leg, ankle, foot and toes) that is caused by running (training or competition). The injury has to be severe enough to cause a reduction in running distance, speed, duration or frequency for at least 7 days or three consecutive scheduled training sessions or the injury requires that the runners consults a physician or other health professional.^46^

Secondary outcome measures include the between-group differences in (1) the severity score of running injuries (range 0 to 100), the proportion of substantial overuse injuries (both based on the OSTRC Overuse Injury Questionnaire) and injury proportion of medical attention injuries, (2) injury proportion in runners with previous injuries and (3) RRI locations.

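### The primary outcome window closes 1 month after the event, but the follow-up questionnaires ask no onset date, so each runner's counting period ends on the day the last one is answered

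*Protocol article*

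**What the plan says.** - **Window.** Outcome measures defines the primary comparison over the time "between the registration for the SPRINT study and 1 month after the running event".
- **Source.** The Abstract (Methods and analysis) names the three follow-up questionnaires as the basis of the compared proportions. Statistical analysis defines the proportion per runner: the percentage reporting a new injury during follow-up.
- **Timing.** Measurements: "Three follow-up questionnaires are sent to the participants (1 month before, 1 week before and 1 month after the running event". The article prints no answering deadline or cut-off.
- **Recall period.** Table 2, follow-up questionnaire: "Running injury since filling in previous questionnaire (yes/no".
- **Timing items in that questionnaire.** The onset item is "Onset (sudden/gradually", which is the manner of onset and not its date. Table 2 also lists "Duration of complaints (weeks" and a yes/no item on complete recovery.
- **Onset date.** "Date onset injury" is listed only for the separate injury questionnaire, which is reached from the biweekly newsletters. Its stated purpose is "To obtain more detailed information about the moment of occurrence of new RRIs".

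**The concern.** The window has a calendar end, while the question that fills it has an open one. Its recall period runs to the moment of answering, and the last questionnaire goes out only when the window closes. A late answer therefore adds counting time, and nothing in that questionnaire directly says whether an injury began before or after the cut-off.

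Answering delay arises after randomisation. Randomisation states that participants are not blinded. A Table 2 footnote shows that only the intervention group's last questionnaire carries the programme section, so the form that closes the window is longer in one arm. The newsletters also differ by arm. A difference in delay is therefore plausible, though the article does not document one. If it exists, the arms are counted over periods of different length.

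Table 2 assigns items to instruments one by one, with footnotes on which questionnaire and arm receive them. The placing of the onset date therefore reads as a design choice and not as shortening for the journal.

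**Working it through.** The plan gives no figure on this point to reproduce. The check has two parts.

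**1. Which injuries stay undated.** Let the cut-off be day 0, let the runner answer on day d, and let complaints have lasted D days.

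- Still present at answering: onset is day d − D, so it lies inside the window if D ≥ d. Duration in weeks dates it to about a week.
- Recovered, D ≥ d: recovery came on or before day d, so onset was on or before day d − D ≤ 0. It lies inside the window.
- Recovered, D < d: onset may fall on either side. This is the ambiguous group.

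The injury definition narrows that group. On the criterion of reduced running for at least 7 days, D is at least 7, so ambiguity needs a delay of more than 7 days. Injuries that qualify through three missed or reduced sessions, or through a consultation, can be shorter.

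**2. Size if delay differs by arm.** Inputs from the article: 38% expected injury proportion and a 5-point difference (Sample size); follow-up of at least 3 months (Statistical analysis); inclusion from August 2019 and data collection to May 2020 (Study design), which bounds follow-up at about 9 months. Assumptions: constant hazard, 38% reached over T = 3, 5 or 8 months, and the delays themselves.

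Hazard per month: λ = −ln(1 − 0.38)/T = 0.478/T.

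Added proportion for d extra days: 0.62 × [1 − exp(−λ × d/30.4)].

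Example, T = 3 and d = 7: λ = 0.1593, and 0.62 × [1 − exp(−0.0367)] = 0.0223, or 2.2 points.

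| Difference in delay between arms | T = 3 | T = 5 | T = 8 |
|---|---|---|---|
| 3 days | 0.97 | 0.58 | 0.36 |
| 7 days | 2.23 | 1.35 | 0.85 |

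Entries are points of shift in the risk difference when one whole arm answers that much later on average.

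The same model can be run with only a share of runners late:

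- A runner 2 weeks late adds 1.68 points (T = 8). If the late share differs by 10 percentage points between arms, the shift is 0.10 × 1.68 = 0.17 points.
- A runner 4 weeks late adds 8.46 points (T = 3). If the late share differs by 20 percentage points, the shift is 0.20 × 8.46 = 1.7 points. This takes every assumed extreme at once.

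**Equal delay.** With 38% against 33%, T = 3 and 7 days in both arms, the first proportion rises by 2.23 points. The second rises by 0.67 × [1 − exp(−(0.4005/3) × 7/30.4)] = 0.0203, or 2.03 points. The difference moves only from 5.0 to about 5.2 points.

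**Limit of the model.** It counts every day of delay as fully exposed. On the 7-day criterion, a runner answering d days late can report onsets only up to about day d − 7, so the figures overstate the injuries that truly began after the cut-off. The same lag applies to a runner who answers on time, so unequal delay still means unequal counting time.

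**The case against.** The strongest reply is that only the right edge is inexact. Recall since the previous questionnaire covers the time from baseline without gaps, the start is anchored because the baseline questionnaire follows consent at once, and the last form goes out when the window closes. Duration and recovery status date many late injuries. The size rests on delays the article does not report. A journal article may also leave answering deadlines and date handling to the full protocol. Finally, most running injuries come on gradually, as step 6 of the programme says, so a recalled date may add little to a duration in weeks.

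Much of this stands, and it limits the weight of the point. It does not remove the mismatch: Table 2 places the onset date in one instrument and leaves it out of those that carry the primary outcome. A deadline in an unseen document would shorten the overrun without dating the injuries.

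Three stronger readings are tempting, and the article does not support them:

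- *A reader might infer that the primary outcome cannot be computed.* It can, per runner, except for injuries close to the cut-off.
- *A reader might infer that reports from the two sources cannot be matched.* Both record the same 13 locations, the OSTRC severity score and complete recovery, and each follow-up report lies between two completion dates. Matching is approximate, and weak mainly for repeat injuries at one site.
- *A reader might infer that an injury reported in both sources counts twice.* Nothing says the sources are pooled, and a second report cannot change a runner's yes/no status.

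**Conclusion.** The point holds as a mismatch between a calendar window and an open recall period, and its weight is modest. The window closes at each runner's answer, and recovered injuries shorter than the answering delay cannot be placed on either side of the cut-off.

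Equal delay mainly shifts the level of both proportions. Bias in the comparison requires delay to differ by arm. The unblinded design and the longer last form for the intervention group make that possible; the article gives no delay data to show it or size it. With a constant hazard, 38% reached over 3 to 8 months, and an assumed difference of 3 to 7 days, the risk difference moves by about 0.4 to 2.2 points against the design difference of 5. The upper end needs the shortest follow-up together with the largest assumed difference, so it should not be quoted as an expected bias.

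**What to change.** 1. Add the onset-date item, already worded for the injury questionnaire, to the three follow-up questionnaires, or at least to the last one.
2. State that primary events are running-related injuries with onset from the baseline questionnaire to the event date plus 1 month.
3. Where the date is missing, derive onset from the completion date, duration of complaints and complete recovery, as in the first part of the working. State in advance how recovered injuries shorter than the delay are handled.
4. If the newsletter reports are also used for injury-level secondary outcomes such as location or severity, first merge them with the follow-up reports by runner, location and onset date.

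The cost is one item and one sentence. Recalled dates are approximate, especially for gradual onset. The rule also does not recover injuries that began just before an on-time answer and had not yet met the 7-day criterion, so a small dependence on delay remains. Reporting answering delay by arm would show whether it matters.

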## Methods

### Study design

The **S**haping up **P**revention for **R**unning **I**njuries in the **N**etherlands using **T**en steps (SPRINT) study is a RCT in recreational runners who are participating in running events in the Netherlands. Half of the participants of the SPRINT study will get access to the prevention programme during the preparation for a running event, while the other half of the participants will follow their regular preparation for the event. The preparations for the SPRINT study started in December 2018 and in August 2019 the first participants are included. The data collection is finalised in May 2020 and the first results are expected by the end of 2020. The flowchart of the design is shown in figure 1.

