### Statistical analysis

Because the follow-up period of this study is at least 3 months, participants who filled out the baseline questionnaire less than 60 days before the running event will be excluded from the analyses. Descriptive statistics and their corresponding SD and frequency distributions will be calculated for all variables. Consistent with the Consolidated Standards of Reporting Trials statement, intention-to-treat analysis will be performed.^47^ Injury proportions, defined as the percentage of runners who reported a new RRI during follow-up, with 95% CIs will be calculated for all participants and for the intervention and control group separately. The injury proportions of the intervention and control group are compared by calculating the difference with 95% CI. Additionally, ORs with 95% CI will be calculated using univariate logistic regression analysis. Adjusted analysis including potential confounders (eg, age, body mass index and earlier injuries) will be performed using multivariate logistic regression analysis. Subgroup analyses are performed for the following characteristics: previous injuries in the 12 months before the trial, sex, running experience, suffering an RRI at baseline, distance of running event registered for and injury locations. Furthermore, the injury proportion of participants in the intervention group who were compliant with the prevention programme will be compared with the injury proportion of the control group. Participants are regarded as compliant if they indicated in the last follow-up questionnaire that they applied at least one of the advices from the prevention programme to their training sessions. Furthermore, an explorative additional analysis on the number of used steps in relation to the injury risk will be performed. All analyses will be performed in SPPS Statistics 25 and p values <0.05 are regarded as statistically significant.

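### The Running Addiction Scale is collected after randomisation and after at least a third of the injury window, so a whole-window association with injury would not show direction

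*Protocol article*

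**What the plan says.** In the Measurements section, the footnotes to Table 2 place the Running Addiction Scale at one time point: "Only included in the first follow-up questionnaire (1 month before the running event"). They also give its purpose: "included to assess whether specific subgroups of runners are more prone to RRIs due to altered running behaviour are present". The wording is awkward, but the aim is to identify subgroups with a higher tendency to injury.

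The scale is not collected earlier. The same section describes the baseline form as follows: "This questionnaire consists of six sections on demographics, training, running events, lifestyle, previous RRIs and health complaints". None of the items in Table 1 is the scale.

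Under Outcome measures, injuries count "in the time period between the registration for the SPRINT study and 1 month after the running event". Under Randomisation, allocation follows completion of the baseline questionnaire. Under Statistical analysis, "participants who filled out the baseline questionnaire less than 60 days before the running event will be excluded from the analyses". That 60-day limit is the shortest lead time an analysed runner can have.

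**The concern.** To ask which runners are more prone to injury, the characteristic has to be measured before the injury. Here the injury window opens at study registration and the scale is answered later. The form that carries the scale also asks about injuries since the last form. For the first part of the window, the score is therefore recorded after the injury it would be used to explain.

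Two routes could distort the association:

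- **Injury to score.** By the protocol's definition, an RRI means curtailed running for a week or three sessions, or a visit to a health professional. A runner who has just been through that may answer a running-behaviour scale differently because of it.
- **Programme to score.** By then the intervention group has had access to the programme and to newsletters that highlight it. Steps 4 and 6 advise on reducing or skipping sessions, so allocation itself may shift the answers.

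What is at stake is the reading of this one ancillary question. If score and RRIs are related over the whole window, the result cannot separate susceptibility from consequence.

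**Working it through.** **Inputs**

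- Scale taken one month, about 30 days, before the event (Table 2 footnotes).
- Window closes one month, about 30 days, after the event (Outcome measures).
- Lead time L = days from baseline questionnaire to event, at least 60 for analysed runners (Statistical analysis). Registration for the study and the baseline questionnaire are treated as the same day, because the form follows consent immediately (Measurements).
- Earliest enrolment: "in August 2019 the first participants are included" (Study design).
- Data collection ends in May 2020 (Study design). With the last form a month after the event, the last event falls in about April 2020. This is an inference, because the article gives no event dates.

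**Reproducing the plan's own figure.** The Statistical analysis section opens: "Because the follow-up period of this study is at least 3 months". The shortest window is 60 + 30 = 90 days, about 3 months. The figure agrees.

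**Share of the window elapsed when the scale is taken**

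Days before the scale = L − 30. Total window = L + 30. Share = (L − 30)/(L + 30).

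| L (days) | Calculation | Share elapsed | Status of L |
|---|---|---|---|
| 60 | 30/90 | 33% | protocol minimum |
| 90 | 60/120 | 50% | illustrative |
| 120 | 90/150 | 60% | illustrative |
| 180 | 150/210 | 71% | illustrative |
| 210 | 180/240 | 75% | illustrative |

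**Upper end, under assumed dates**

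- Enrolment 31 August 2019, event 1 April 2020: L = 214, 184/244 = 75%.
- Enrolment 1 August 2019, event 30 April 2020: L = 273, 243/303 = 80%.
- August 2019 enrolment, event on 31 December 2019 (the latest possible 2019 date): L = 122 to 152, giving 92/152 = 61% to 122/182 = 67%.

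**From time to injuries (illustration only).** Assume a constant hazard and the 38% incidence used in the Sample size section. The proportion injured before the scale is then 1 − 0.62^share. Dividing by 0.38 gives the fraction of first injuries that precede it.

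- L = 60: 1 − 0.62^(30/90) = 0.147, and 0.147/0.38 = 39%.
- L = 240: 1 − 0.62^(210/270) = 0.311, and 0.311/0.38 = 82%.

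**What is left after the scale.** Every analysed runner has about 30 + 30 = 60 days of window remaining. With the scale at baseline, the elapsed share would be 0%.

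**The case against.** The strongest reply is that no analysis described in the article depends on the scale. It is not a primary or secondary outcome, it is not in the subgroup list under Statistical analysis or the one in the Discussion, and it is not among the example adjustment variables. How it will be analysed may be set out in a fuller document. This stands, and it limits the point to an ancillary question.

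A reader might infer that the scale cannot answer its question at all. The documents do not support that. Each follow-up form covers injuries since the one before, and the separate injury questionnaire records the date of onset. A forward-looking analysis over roughly the last 60 days, including the event itself, is possible with the data as planned. The article also does not say that the score will be related to earlier injuries.

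A reader might also infer that the scale fails as a subgroup variable for the treatment effect. The article never proposes that use, so there is nothing to fail.

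The footnote's phrase about altered running behaviour could mean behaviour during preparation for the event, in which case the timing may be deliberate. The text does not settle this. Even on that reading, injuries before the scale need separating from those after it. If running addiction were a stable trait the distortion would be smaller, but the document does not say that it is.

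Finally, only the one-third figure follows from the text. The higher shares depend on lead times and event dates that the article does not give.

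**Conclusion.** The concern holds as a minor design weakness. The stated timing does not fit the stated purpose: a score meant to identify runners prone to injury is taken after randomisation and after at least one third of the injury window (30 of 90 days, with a month taken as 30 days). For earlier enrollees the share is larger, about 75–80% for August 2019 enrolment if the last event is assumed to be in April 2020. These are shares of time. The 39% to 82% of first injuries applies only under the assumed constant hazard and 38% incidence.

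An association over the whole window could reflect an effect of injury or of the programme on the score. An association restricted to later injuries is not open to the first of these. The primary and secondary comparisons between arms are untouched.

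**What to change.** Move the Running Addiction Scale to the baseline questionnaire, so that it precedes both randomisation and the injury window. The cost is a slightly longer baseline form.

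For runners already enrolled, state that the score will be related only to new RRIs reported on the second and third follow-up questionnaires, among runners with no RRI up to the first, with adjustment for arm. This needs only a change of wording and no new data. Its cost is fewer usable events: under the constant-hazard illustration, 100 − 39 = 61% of first injuries remain at a 60-day lead time and 100 − 82 = 18% at 240 days. The result would also apply only to runners who reached the first follow-up uninjured.
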